## Introduction

The Developmental Origins of Health and Disease (DOHaD) hypothesis^1 2^ proposes that early life exposures along with postnatal environmental factors (childhood experiences, education, nutrition, infections, lifestyle, socioeconomic conditions) determine risk for disease in later life. Recent investigations suggest an early life origin of neurodevelopmental disorders (autism spectrum disorders, depression, schizophrenia).^3^ Early intrauterine insults can impact development of brain areas that show high neuronal growth such as hippocampus and cortical areas.^4^ Later life factors influence synaptic pruning and myelination.^5^ Altered brain structural and functional connectivity within and between hippocampal, frontal and subcortical networks is known to be associated with impaired neurocognitive functioning and neurodevelopmental disorders.^6 7^

The growing fetus is wholly dependent on the mother for its nutrition. Deficiency of various micronutrients in the mother during critical phases of fetal development can affect organ structure and function, hence programming the risk for chronic disease in later life (fetal programming).^8^ Recently, there is considerable interest in the role of maternal vitamin B_12_ and folate in fetal programming.

Vitamin B_12_ is important for nerve myelination and its deficiency is associated with subacute combined degeneration of spinal cord, depression and dementia.^9^ The role of folate deficiency in risk for neural tube defects (NTDs) is well known. Both these vitamins influence the one carbon metabolism cycle.^10^

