In India, vitamin B_12_ deficiency is widely prevalent in women in the reproductive age group while rates of folate deficiency are low.^22–24^ The vitamin B_12_ deficiency is attributable to practice of vegetarianism and low socioeconomic status. Public health policy mandates only iron-folic acid supplementation in adolescents and pregnant women. It is also a common clinical practice to supplement high dose folic acid (5 mg) to pregnant women to prevent NTD. This scenario inadvertently promotes an imbalance between vitamin B_12_ and folate status during the pregnancy,^19 25^ which could enhance risk of adverse health outcomes in the offspring including aberrant neurodevelopment. In the presence of vitamin B_12_ deficiency, folate is trapped in its unusable methyl form and methyl groups are unavailable for further biochemical reactions. This interferes with important cell processes such as purine pyrimidine synthesis, DNA repair and epigenetic regulation (DNA methylation). Unavailability of methyl groups prevents conversion of homocysteine to S-adenosyl methionine leading to hyper-homocysteinaemia which can adversely affect vascular endothelial and placental function. Indiscriminate supplementation in the presence of vitamin B_12_ deficiency leads to accumulation of unmetabolised folic acid, which is known to have neurotoxic effects.^25 26^ Animal experiments performed in India have examined the role of a maternal vitamin B_12_-folate micronutrient imbalance and show that offspring dams of mothers fed on a low vitamin B_12_-highfolate diet have poorer spatial memory functions, lower brain hippocampal weight, reduced neurotrophic factor BDNF and reduced TRK gene expression.^27 28^ However, no study in India has examined long-term effects of maternal vitamin and folate during the pregnancy on offspring neurodevelopmental outcomes in young adulthood.

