### Hypotheses

We hypothesise that a lower maternal vitamin B_12_, higher folate, higher homocysteine nutrient pattern during pregnancy adversely impacts development of brain regions. This will be reflected in brain imaging as reduced brain volume as measured through anatomical images, weaker connections in structural/functional networks (hippocampal and frontal-subcortical connections) involved in cognitive processing (memory, executive functions) as measured through DTI and rsfMRI, respectively. These structural and functional changes will in turn result in poorer neurodevelopmental outcomes (lower neuropsychological test performance, adverse temperamental traits and higher risk for common mental disorders) in the young adult offspring.’

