### Assessments

The exposures and outcome measurements are summarised in table 1.

**Table 1 T1:** Exposures and outcomes defined in the study

	Exposures	Tests	Variables measured
1.	Maternal Micronutrient status and homocysteine at 18 and 28 weeks pregnancy	Biochemical assays	Vitamin B_12_, red cell folate, homocysteine

	Outcomes	Tests	Variables measured
1.	Neurocognitive performance	WAIS-IV WMS AVLT Colour Trails test	Verbal comprehension, perceptual reasoning, working memory, processing speed, Full scale IQ. Immediate memory, delayed memory and working memory. Errors in immediate and delayed recall time taken and errors for colour trails test A and B.
2.	Temperament	Adult Temperament Questionnaire	Negative affect, extraversion, orienting sensitivity, effortful control
3.	Common mental disorders	Brief Symptom Inventory Mini Neuropsychiatric Interview 7.0 for DSM 5 diagnosis	Global severity index DSM 5 diagnosis of past or current major depressive disorder, suicidality, panic disorder, agoraphobia, social anxiety disorder, generalised anxiety disorder
5.	Brain Imaging	Structural T1 MPRAGE Resting state fMRI Diffusion tensor imaging	Cortical volume and thickness Resting state functional connectivity tractography, FA and MD values in relevant white matter tracts
	Life course variables		
	Birth		Birth weight, length, head circumference, sum of skin folds
	Later life growth and development		Height, BMI, head circumference sum of skin folds at 6, 12, 18 years
	Later life nutrition		Haemoglobin, vitamin B_12_, folate, homocysteine, ferritin, glucose, lipids at 6,12,18 years
	Socioenvironmental		Mothers education, fathers education, standard of living index, adverse childhood experiences.

AVLT, auditory verbal learning test; BMI, body mass index; DSM, Diagnositic and Statistical Manual of Mental Disorders; FA, fractional anisotropy; fMRI, functional MRI; MD, mean diffusivity; WAIS-IV, Wechsler’s Adult Intelligence Scale IV; WMS, Wechsler Memory Scale.

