
For each modality, the following statistical comparisons will be performed. We will first perform correlations between maternal vitamin B_12_ and folate exposures with brain MRI outcomes to examine for any linear relationships. We will use an analysis of covariance model to examine differences in MRI outcomes between low and high maternal vitamin B_12_ groups. Similarly, we will examine for differences between low and high maternal red cell folate groups (selected based on median value of maternal red cell folate) and for any interaction between maternal vitamin B_12_ and folate status. Variance due to subjects’ age, gender, total intracranial volume, ACEs will be regressed out of the analyses. Effects of additional factors (such as current vitamin B_12_ status of offspring, education status, socioeconomic status) will be examined.

For making inferences from multimodal imaging data, we will adopt a hierarchical approach. Accordingly, we will perform voxel-wise tests for difference in grey matter volume (or cortical thickness). For brain regions which are significant, DTI-based structural connectivity and fMRI-based functional connectivity between those regions will be investigated. This strategy assures that the effects of interest have both structural and functional aetiologies, and hence are likely to be robust and reproducible.

#### Objective 3

This examines causality of association between maternal nutritional factors and neurocognitive outcomes. The genetic determinants of vitamin B_12_ have been described in our population using GWAS,^36^ which will be used to calculate a gene risk score of vitamin B_12_ deficiency. Mendelian randomisation analysis (triangulation and instrumental variable analysis) using the genetic risk score for vitamin B_12_ deficiency and homocysteine (MTHFRrs1801133) will be performed.

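### The core imaging model does not commit to adjusting for socioeconomic status, which the protocol links to low B12 and to later disease risk; volume should also be reported without intracranial volume

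*Protocol article*

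**What the plan says.** Protocol article, Plan of data analysis, Objective 2: for each imaging modality, an analysis of covariance compares the low and high maternal B12 groups, and "age, gender, total intracranial volume, ACEs will be regressed out of the analyses". The next sentence reads "Effects of additional factors (such as current vitamin B_12_ status of offspring, education status, socioeconomic status) will be examined". It does not say whether the main comparison will carry these factors as covariates.

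Other parts of the same document bear on this:

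- Introduction, on the exposure: "The vitamin B_12_ deficiency is attributable to practice of vegetarianism and low socioeconomic status".
- Introduction, on later outcomes, listing postnatal environmental factors: "childhood experiences, education, nutrition, infections, lifestyle, socioeconomic conditions) determine risk for disease in later life".
- Assessments, Table 1, socioenvironmental row: "Mothers education, fathers education, standard of living index, adverse childhood experiences".
- Hypotheses: the imaging effect is expected to appear as "reduced brain volume as measured through anatomical images". The preceding sentence speaks of the development of brain regions.
- Subject selection: the two groups are mothers below 103 pM and above 175 pM at 18 weeks, given as the outer quartiles.

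**The concern.** The low and high B12 groups are extremes of an observed exposure. Random selection of 100 participants within each group does nothing to balance the groups on other characteristics. A factor that lowers maternal B12 and also affects the offspring's brain would produce a group difference without any effect of B12. On the protocol's own account, socioeconomic status is a candidate for that role. Childhood adversity, from the same row of Table 1, is in the core set. The standard of living index and parental education are not. As written, whether the headline estimate is adjusted for them could be settled after the results are seen.

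A second, smaller concern is total intracranial volume. It reflects early head and brain growth, so an exposure acting in fetal life may itself change it. Where the hypothesis is lower brain volume, conditioning on intracranial volume can take out part of the effect sought. The plan describes no total brain or total grey matter volume outcome and no volume analysis without the term.

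**Working it through.** **Yardstick.** Power estimation states 80% power for an effect size of 0.3 with 100 per group at p<0.05. Read as a difference of 0.3 SD, two-sided: Φ(0.3 × √(100/2) − 1.96) = Φ(0.161) = 56%. The stated 80% does not reproduce on that reading. That is a separate matter; 0.3 is used here only as the size of effect the study had in mind.

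**Step 1: socioeconomic status left out of the model.** Let *a* be its correlation with maternal B12 and *b* its correlation with the imaging outcome. Both are assumptions; the documents give neither. Suppose B12 has no effect and the variables are roughly normal.

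- Outer-quartile groups of a normal exposure differ in mean by 2 × φ(0.674)/0.25 = 2 × 1.271 = 2.542 SD.
- The correlation of B12 with the outcome that runs through socioeconomic status is *ab*, so the spurious difference is *d* = 2.542 × *a* × *b*.
- The rejection rate is that of a two-sided 5% t-test with 198 degrees of freedom and non-centrality *d* × √(100/2).

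| a | b | d (SD) | Type I error |
|---|---|---|---|
| 0.1 | 0.1 | 2.542 × 0.01 = 0.03 | 5.4% |
| 0.1 | 0.2 | 2.542 × 0.02 = 0.05 | 6.5% |
| 0.2 | 0.2 | 2.542 × 0.04 = 0.10 | 11% |
| 0.2 | 0.3 | 2.542 × 0.06 = 0.15 | 19% |
| 0.3 | 0.3 | 2.542 × 0.09 = 0.23 | 36% |

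The results are for one outcome, and they assume that childhood adversity in the core model absorbs none of the imbalance.

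**Step 2: intracranial volume in the model.** Take a true deficit of 0.3 SD in brain volume. Let *r* be the assumed correlation of volume with intracranial volume and *t* the fall in intracranial volume, in SD. The adjusted difference is 0.3 − *r* × *t*, and the residual SD is √(1 − *r*²). Power is for 100 per group, two-sided 5%.

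| r | t = 0 (regional deficit) | t = 0.15 | t = 0.3 (proportionate global deficit) |
|---|---|---|---|
| 0.7 | 0.30 SD, power 84% | 0.195 SD, 49% | 0.09 SD, 14% |
| 0.8 | 0.30 SD, power 94% | 0.18 SD, 56% | 0.06 SD, 11% |
| 0.9 | 0.30 SD, power 99.8% | 0.165 SD, 76% | 0.03 SD, 7% |

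Without the term, power for 0.3 SD is 56% throughout. Adjustment is therefore a clear gain when intracranial volume is unaffected, can lose or gain when it is partly affected, and loses most of the effect when it falls in step.

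**The case against.** **Socioeconomic status.** A reader might infer that the plan ignores it. It does not: the text commits to examining its effects, which can be read as a base model followed by an extended one. The protocol also never calls it a confounder of brain outcomes. The B12 statement concerns India and names vegetarianism first, the outcome statement concerns disease risk in general, and no association within this six-village cohort is given. With correlations of 0.1 and 0.1 the bias is negligible, and adjustment for childhood adversity may absorb some of it. All this stands, and it rules out saying that the contrast *is* confounded. It does not answer the narrower point. The article fixes a core covariate set, which is more than leaving detail to an analysis plan, and that set lacks a measured candidate common cause.

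**Intracranial volume.** A reader might infer that the plan cannot detect its own hypothesis. The documents do not support that. The hypothesis begins with brain regions, and the planned structural outcomes are regional: voxel-wise tests, 68 cortical parcels and 11 hippocampal subfields. For these the adjustment is standard, preserves a regional deficit and gains precision. Nor do the documents show harm from the term in the thickness, diffusion or functional models; removing it there would be a preference. What remains is that the hypothesis of reduced brain volume can also be read globally, and the plan describes no analysis for that reading.

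**Conclusion.** The point holds in conditional form. The main low-versus-high B12 imaging contrast is not committed to adjustment for socioeconomic status, and it may be confounded for that reason. Over assumed correlations of 0.1 to 0.3, the consequence runs from negligible to a spurious difference about three quarters of the 0.3 that the study was sized for (0.23/0.3 = 0.76). The direction, exaggerating harm from low B12, further assumes that disadvantage goes with both lower B12 and poorer brain outcomes. Because Objective 2 opens connectivity testing only for regions significant on volume or thickness, a false signal at the first stage would also steer the later ones.

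The intracranial volume point is secondary. It matters only if the deficit is wholly or largely global; for regional outcomes the planned adjustment is sound.

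**What to change.** In Plan of data analysis, Objective 2, move the standard of living index and mother's and father's education into the core covariate set of every imaging model, so that the headline B12 contrast is the adjusted one. Current offspring B12 can remain a factor for further examination.

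Keep intracranial volume in the regional volume models. Add total brain or total grey matter volume, analysed without that term, as the test of a global reduction, and describe the adjusted regional results as tests of disproportionate change.

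The cost is a few degrees of freedom out of about 200 scans, some wording and one extra set of model runs. No new data are needed for the covariates, and the volumes come from images already planned or acquired.

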### Image acquisition

For structural imaging, 3D T1-weighted MPRAGE images will be acquired (TR=2300 ms, TE=2.26 ms, TI=900 ms, Flip angle=8 °, slice thickness=1 mm, in-plane resolution=1×1 mm^2^, GRAPPA parallel imaging with acceleration factor of, 192 slices, FOV readout=256 mm, FOV phase encoding=100%, and acquisition time of 5 min and 21 s).

For functional imaging, T2*-weighted echo-planar imaging sequence will be used to acquire BOLD fMRI data while participants are resting with eyes open and fixated, and not thinking about anything specific. A rsfMRI scan helps to characterise brain-wide networks from a single scan as opposed to task-based fMRI which characterises evoked responses in specific brain systems. Thirty-six axial slices will be acquired covering the whole brain with a slice thickness of 3 mm, in-plane resolution of 3×3 mm^2^, TR=2000 ms; TE=30 ms; flip angle=90^0^, FOV readout=256 mm, FOV phase encoding=100%, GRAPPA parallel imaging with acceleration factor of, and 300 measurements with an acquisition time of 10 min and 8 s. Prospective acquisition correction (PACE) motion correction will be employed in this sequence.^33 34^

Diffusion-weighted images will be acquired using the RESOLVE sequence given its robustness against susceptibility artefacts. Scan parameters for RESOLVE will be: Thirty-six axial slices covering the whole brain with a slice thickness of 3 mm, in-plane resolution of 1.4×1.4 mm^2^, TR=5460 ms; TE=73/109 ms; flip angle=180°, FOV readout=220 mm, FOV phase encoding=100%, GRAPPA parallel imaging with acceleration factor of 2, 30 diffusion directions, two diffusion weightings (b values) of 0 and 1000 s/mm^2^ and an acquisition time of 14 min and 19 s.

All MRI images will be visually inspected for quality assessment and reviewed by a radiologist to rule out any structural abnormalities.

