Structural brain MRI analysisVoxel-based morphometry on T1 MPRAGE anatomical images will be performed using statistical parametric mapping in Matlab. Preprocessing steps will involve coregistration, segmentation. Spatial normalisation will transform all subject data to the same stereotactic space. Grey matter images will be smoothed by convolving with an isotropic Gaussian kernel. Statistical analysis using general linear model will be used to identify regions of grey matter concentration that are significantly associated with our exposures of interest.Cortical volume, thickness and hippocampal segmentation: A surface-based morphometric technique will be employed to measure cortical volume and thickness. We will use FreeSurfer software for image analysis. Standard steps include intensity normalisation, skull stripping and removal of non-brain tissues followed by segmentation, topology correction, registration and automated parcellation. Cortical volume and thickness will be computed for 68 regions (34 in each hemisphere) using the Desikan-Kelliany Atlas. The hippocampal subfield segmentation tool in FreeSurfer will be employed to compute volumes of the various hippocampal structures as per the inbuilt atlas which defines 11 hippocampal subfield structures.Structural connectivity—diffusion tractography analysis: Diffusion-weighted images will be analysed using the ‘The Diffusion Toolbox’ software tool in the FMRIB Software Library (FSL; http://www.fmrib.ox.ac.uk/fsl/fdt/index.html). After preprocessing including motion correction and eddy current correction, the DTI indices fractional anisotropy, mean diffusivity (MD) and radial diffusivity will be computed. Structural connectome generation will be performed on the MRItrix3 software. Preprocessing steps will involve denoising and correction for eddy currents. The b0 volume of preprocessed images will be extracted and registered to the T1 image using FSL’s BET tool. The fibre orientation dispersion functions (FODs) will be generated for white matter and normalised. Probabilistic streamlines tractography will be performed by dynamically seeding the normalised white matter FOD’s. The whole brain tractogram thus generated will be used for structural connectome generation.Functional connectivity: CONN software (https://web.conn-toolbox.org/) will be used for the analysis of rsfMRI data. This will involve standard preprocessing steps such as realignment, normalisation to MNI space, elimination of temporal linear trends and regressing out nuisance covariates such as residual motion and physiological artefacts. aCompCor will be used for minimising physiological artefacts. Motion censoring and interpolation will also be used to remove the effects of large frame wise displacements due to head motion. Following preprocessing, mean time series will be extracted from 91 cortical and 15 subcortical regions in the FSL Harvard-Oxford atlas, as well as from 26 cerebellar regions in the AAL atlas. These time series will be used in a whole brain functional connectivity analysis employing Pearson’s correlation coefficient between the mean time series.

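### The group models for resting-state and diffusion MRI include no participant-level head-motion covariate, so residual motion that differs between the B12 groups could confound connectivity differences

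*Protocol article*

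**What the plan says.** The statistical comparisons for Objective 2 (Plan of data analysis) are common to all imaging: "For each modality, the following statistical comparisons will be performed". The main contrast is stated as "We will use an analysis of covariance model to examine differences in MRI outcomes between low and high maternal vitamin B_12_ groups". The adjustment is for age, "gender, total intracranial volume, ACEs will be regressed out of the analyses". The same paragraph covers the red cell folate comparison and the B12-by-folate interaction. It then adds an open list: "Effects of additional factors (such as current vitamin B_12_ status of offspring, education status, socioeconomic status) will be examined".

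Motion is dealt with earlier in the pipeline:

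- **Resting-state fMRI, acquisition** (Image acquisition): "Prospective acquisition correction (PACE) motion correction will be employed in this sequence".
- **Resting-state fMRI, preprocessing** (Functional connectivity): realignment, then "regressing out nuisance covariates such as residual motion and physiological artefacts", then "Motion censoring and interpolation will also be used to remove the effects of large frame wise displacements due to head motion".
- **Diffusion, tensor indices** (Structural connectivity): "After preprocessing including motion correction and eddy current correction", the FA, MD and radial diffusivity values are computed.
- **Diffusion, connectome** (same section): the listed preprocessing is denoising and eddy-current correction; motion is not named.
- **All images** (Image acquisition): visual quality inspection, with no motion threshold given.

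**The concern.** Every motion control listed acts on one participant's scan at a time. Such steps reduce the effect of movement. They do not adjust for differences between participants in average small movement. Censoring targets large displacements, and it leaves participants with different amounts of usable data. A difference between exposure groups in what remains would pass straight into the group contrast, because nothing in the between-participant model represents it.

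This study has a particular reason to care. The Hypotheses section expects poorer executive function and weaker hippocampal and frontal-subcortical connections after a low-B12 nutrient pattern. Lying still through a resting-state scan of 10 min 8 s and a diffusion scan of 14 min 19 s plausibly draws on the same attention and control, so motion could differ by exposure group. A connectivity difference arising from movement might then be read as support for the hypothesis.

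**Working it through.** **Plan's own figure.** The article gives no figure on motion. Its only figure for this contrast is the power statement (100 per group, effect size 0.3, 80% power). Only the group size is used below. Read as a two-sided comparison of standardised means, that statement gives 56.4% rather than 80%; this is a separate matter and nothing here depends on it.

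**Step 1: which controls reach the group model.**

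| Outcome | Within-scan motion control named | Motion term in group model |
|---|---|---|
| Resting-state connectivity | Prospective correction, realignment, residual-motion regression, censoring | None |
| FA, MD, radial diffusivity | Motion and eddy-current correction | None |
| Diffusion connectome | None named (denoising and eddy currents only) | None |

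**Step 2: size of the possible bias.** Inputs:

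- n = 100 per group (Power estimation).
- ρ = correlation between motion and connectivity left after cleaning. Assumed 0 to 0.3.
- d = difference in mean motion between B12 groups, in SD. Assumed 0.1 to 0.5.

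Formulae, with no true connectivity difference:

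- bias = ρ × d (in SD of connectivity)
- SE = √(2/100) = 0.141
- type I error = Φ(bias/SE − 1.96) + Φ(−bias/SE − 1.96)

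Worked for ρ = 0.3, d = 0.5: bias = 0.15; bias/SE = 1.06; error = Φ(−0.90) + Φ(−3.02) = 18.6%.

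| ρ | d = 0.1 | d = 0.2 | d = 0.3 | d = 0.5 |
|---|---|---|---|---|
| 0 | 0 SD, 5.0% | 0 SD, 5.0% | 0 SD, 5.0% | 0 SD, 5.0% |
| 0.1 | 0.01, 5.1% | 0.02, 5.2% | 0.03, 5.5% | 0.05, 6.4% |
| 0.2 | 0.02, 5.2% | 0.04, 5.9% | 0.06, 7.1% | 0.10, 10.9% |
| 0.3 | 0.03, 5.5% | 0.06, 7.1% | 0.09, 9.8% | 0.15, 18.6% |

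**Step 3: price of adjusting.** With equal groups, the squared correlation between group and motion is (d²/4)/(1 + d²/4), so the variance inflation is 1 + d²/4. For d = 0.1 this is 1.0025; for d = 0.5 it is 1.0625. If the motion effect is linear and motion is measured without error, the covariate removes the bias; otherwise it reduces it.

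**The case against.** **Layered control is already planned.** Prospective correction, realignment, residual-motion regression, censoring and visual inspection leave only residual motion to confound. This stands. It is why the range above starts at zero, and at ρ = 0.1 the error is only 5.1% to 6.4%.

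**An article condenses.** Second-level covariates may sit in a fuller document, and the list of additional factors is open. This stands in part: the connectome steps, for instance, may be shorthand. But the article does state a covariate set for every modality, its examples of further factors are biological or social, and those are only to be examined.

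**Connectivity tests are gated.** In the hierarchical approach, connectivity is investigated only between regions already significant on grey matter. This stands against any whole-brain count. A reader might take the 91 + 15 + 26 = 132 regions, form 132 × 131/2 = 8,646 pairs and multiply by an inflated error rate. The documents do not support that: the gate limits how many connections are tested, and nothing shows the same motion correlation in every pair. The gate does not remove the bias in those connections that are tested, and the grey-matter step uses the same covariate list.

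**Motion may be a consequence of exposure.** If low B12 impairs control and so increases movement, adjustment could remove part of a true effect. This is a fair point. Adjustment moves the estimate by the same product ρ × d, whichever interpretation is right, so both results need to be shown.

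**Conclusion.** The omission is real and worth correcting: no participant-level motion measure enters the resting-state or diffusion group models, and the text gap is clearest for the diffusion connectome. Residual motion could therefore confound the B12 comparison. Under the assumed ranges the bias is 0 to 0.15 SD, against a planned effect size of 0.3, and the per-test type I error is 5.0% to 18.6%. The lower end applies if cleaning is complete; the upper end needs both assumed values at their maximum.

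A reader might infer that a motion difference would show up as weaker connectivity in the low-B12 group. The documents do not support that. It would require more movement in that group, an effect that survives cleaning, and a weakening effect on the specific hippocampal and frontal-subcortical connections. None of these is given. The supportable statement is that confounding is possible and might run in the hypothesised direction.

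**What to change.** - Add mean framewise displacement as a covariate in the group models for resting-state and diffusion outcomes, taken from each sequence's own motion correction. For fMRI, also add the share of frames kept after censoring.
- Report both measures by B12 group.
- Give results with and without the motion covariates, because motion may partly be a consequence of exposure.
- Include motion correction in the connectome preprocessing, as in the FA/MD pipeline, or say so if it is already meant.

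No new data are needed: motion correction already yields displacement. With 195 of the intended 200 scans obtained by March 2020, the analysis is where this can still be handled. The cost is one or two degrees of freedom, a variance inflation of at most about 1.06 over the assumed range for the displacement term, and possibly some conservatism, slight over most of that range.
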